## Abstract

**Background:**

Postoperative delirium (POD) is a manifestation of acute postoperative brain dysfunction that is frequently observed after cardiac surgery. POD is associated with short-term complications such as an increase in mortality, morbidity, costs and length of stay, but can also have long-term sequelae, including persistent cognitive deficits, loss of independence, and increased mortality for up to 2 years. The noble gas xenon has been demonstrated in various models of neuronal injury to exhibit remarkable neuroprotective properties. We therefore hypothesize that xenon anesthesia reduces the incidence of POD in elderly patients undergoing cardiac surgery with the use of cardiopulmonary bypass.

**Methods/Design:**

One hundred and ninety patients, older than 65 years, and scheduled for elective cardiac surgery, will be enrolled in this prospective, randomized, controlled trial. Patients will be randomized to receive general anesthesia with either xenon or sevoflurane. Primary outcome parameter will be the incidence of POD in the first 5 postoperative days. The occurrence of POD will be assessed by trained research personnel, blinded to study group, with the validated 3-minute Diagnostic Confusion Assessment Method (3D-CAM) (on the intensive care unit in its version specifically adapted for the ICU), in addition to chart review and the results of delirium screening tools that will be performed by the bedside nurses). Secondary outcome parameters include duration and severity of POD, and postoperative cognitive function as assessed with the Mini-Mental State Examination.

**Discussion:**

Older patients undergoing cardiac surgery are at particular risk to develop POD. Xenon provides remarkable hemodynamic stability and has been suggested in preclinical studies to exhibit neuroprotective properties. The present trial will assess whether the promising profile of xenon can be translated into a better outcome in the geriatric population.

**Trial registration:**

EudraCT Identifier: 2014-005370-11 (13 May 2015).

## Background

Postoperative delirium (POD) is frequently observed after cardiac surgery with incidences ranging from 20 to 80 % [1, 2]. It is associated with short-term complications such as an increase in mortality, morbidity, costs and length of stay, but is also associated with long-term sequelae, including the development of persistent cognitive deficits, loss of independence, and increased mortality for up to 2 years [3].

The pathophysiology of POD is complex and thought to be related to cerebral ischemia-reperfusion injury, endothelial dysfunction [4], neuroinflammation [5], neurotransmitterimbalances [6, 7] and direct neurotoxic effects of anesthetics [8]. The individual baseline risk of a patient to develop POD is determined by a variety of predisposing factors that are not possible to be modified, including age, male gender, psychiatric illness, cognitive impairment (e.g. dementia) and atherosclerotic disease [2].

POD has been suggested to be precipitated by intraoperative and postoperative triggers. In contrast to the predisposing factors, precipitating factors are amenable to modification and have thus become a target of prevention strategies. Unfortunately, the unambiguous identification of precipitating factors for POD remains notoriously difficult. Numerous elements have been described, including (but not limited to) cardiovascular surgery, use of cardiopulmonary bypass (CPB), application of anesthetics and cognitively active medication, hypotension, decreased cardiac output, hypothermia and hypoxia [9, 10].

The noble gas xenon has been shown to offer neuroprotection in numerous in-vitro and in-vivo models of neuronal injury including models of post-cardiac surgery neurocognitive dysfunction [11, 12]. Neuroprotection by xenon is most likely achieved by diverse mechanisms including antagonism at the N-methyl-D-aspartate (NMDA) subtype of the glutamate receptor [13], an enhanced synthesis of prosurvival (B-cell lymphoma 2 and extra large) proteins and the suppression of neuronal apoptosis [14, 15]. Moreover, xenon preserves cerebral flow-metabolism coupling [16, 17] and possesses anti-inflammatory qualities that may directly interfere with the pathogenesis of POD [18]. Furthermore, the favorable physicochemical properties of xenon result in rapid clearance from the brain, thereby reducing any residual anesthetic effects that may predispose to POD [19, 20]. Last, xenon has been repeatedly demonstrated to cause less hemodynamic deterioration than conventionally used anesthetics [21–23]; therefore, it helps to avoid hemodynamic instability which is a precipitating factor for POD.

Therefore, we hypothesize that in older cardiac surgical patients, the use of xenon anesthesia significantly reduces the incidence of POD when compared to the conventionally used anesthetic sevoflurane. Additionally, the evaluation of outcome will include several secondary endpoints such as the duration and severity of POD, postoperative cognitive function as analyzed with the Mini-Mental State Examination (MMSE), length of intensive care unit (ICU) stay, hospital length of stay, the incidence of postoperative organ dysfunction and the incidence of (serious) adverse events ((S)AE).

## Methods/Design

### Study registration

The study will be performed according to the principles of the International Declaration of Helsinki and to the principles of good clinical practice (GCP) and is approved by the ethics committee of the University Hospitals Leuven, by the Clinical Trials Centre of the University Hospital Leuven, and by the “Federaal Agentschap voor Geneesmiddelen en Gezondheidsproducten.” The study is registered in the European Clinical Trials Database of the European Medicines Agency (EudraCT Identifier: 2014-005370-11, 13 May 2015). Any eventual changes of the study protocol will be reported to the ethics committee.

### Recruitment

Patients will be recruited by the principal investigator or co-investigator. Detailed information about the study background and protocol will be given, and any possible questions brought forward by the patients will be answered. Each eligible patient who is willing to participate in the study will sign a written informed consent before any particular study procedure.

### Study type

This prospective, randomized, controlled trial will be performed at the University Hospital of the KU Leuven by two types of investigators. Investigator I will assess the primary outcome (and the majority of the secondary outcome parameters) and is blinded to the group affiliation. Investigator II will perform anesthesia and cannot be blinded to the treatment groups due to the administration of the anesthetic via a dedicated anesthesia machine and the mandatory monitoring of anesthetic concentrations [24].

### Randomization

Patients will be randomized using a computer-generated permuted block randomization sequence (variable block-size, 1:1 allocation). Randomization will be stratified by the European System for Cardiac Operative Risk Evaluation (EuroSCORE) II (Stratum I: EuroSCORE ≤ 3; Stratum II: EuroSCORE > 3). A masked randomization procedure will be used in which group assignments are hidden in sealed, opaque, sequentially numbered envelopes that will only be opened upon arrival of the patient to the operation room (OR).

### Inclusion criteria

Age > 65 yearsPatient scheduled for elective heart surgery with the use of CPBAble to read and understand the research materials

### Exclusion criteria

Inability to give informed consentIntraoperative need for one-lung-ventilation and/or for an increased fraction of inspired oxygen (FiO_2_ > 50 %)Chronic obstructive pulmonary disease (COPD) GOLD > IICritical preoperative state (as defined by the requirement of inotropic support or intra-aortic balloon pump (IABP), ventricular tachycardia or ventricular fibrillation, preoperative cardiac massage, preoperative ventilation before anesthetic room, preoperative acute renal failure (anuria or oliguria < 10 ml hr^−1^) [25]Disabling neuropsychiatric diseases (dementia, schizophrenia, epilepsy or mental retardation)Presence of delirium at baseline as screened with the 3-minute Diagnostic Confusion Assessment Method (3D-CAM) [26]Alcohol abuse: (defined as a CAGE score ≥ 2) [27]History of drug abuseHistory of stroke or traumatic brain injury with residualsIncreased intracranial pressureHypersensitivity to the study medicationsRisk for malignant hyperthermia

### Anesthesia and intervention

The different steps of the study visits are summarized in Fig. 1.

**Fig. 1 Fig1:**
[figure not shown]
Schematic illustration of the study visits. 25-OHD, 25-hydroxy vitamin D; 3D-CAM, 3-minute Diagnostic Confusion Assessment Method; AE, adverse event; APACHE II, Acute Physiology and Chronic Health Evaluation II; BIS, bispectral index; CAM-S, Confusion Assessment Method Severity score; CCI, Charlson Comorbidity Index; DOS, Delirium Observation Scale; GDS, Geriatric Depression Scale; ICDSC, Intensive Care Delirium Screening Checklist; ICU, intensive care unit; IL, interleukin; IQCODE, Informant Questionnaire on Cognitive Decline in the Elderly; Katz ADL, Katz Index of Activities of Daily Living; MMSE, Mini-Mental State Examination; NIRS, near-infrared spectroscopy; RASS, Richmond Agitation-Sedation Scale; SAPS, Simplified Acute Physiology Score; SOFA, Sequential Organ Failure Assessment score; SAE, serious adverse events; TEE, transesophageal echocardiography

#### Baseline assessment (Investigator I)

Investigator I will obtain written informed consent and record baseline data (demographic data, medical and surgical history, routine clinical examination, Charlson comorbidity index (CCI) [28], results of preoperative chest X-ray, electrocardiogram (ECG) analysis, echocardiography and standard laboratory parameters). In addition, the MMSE [29], the 3D-CAM, the Geriatric Depression Scale (GDS) [30] and an interview with a family member using the short form of the Informant Questionnaire on Cognitive Decline in the Elderly (IQCODE) [31] will be performed the day before surgery. Patients with alcohol abuse will be identified with the CAGE questionnaire [27] and excluded. Besides, patients’ preoperative functional status will be assessed using the Katz Index of Activities of Daily Living (ADL) [32].

#### General anesthesia

Patients must be in a fasting state for 6 hours prior to anesthesia. Patients will be premedicated with lorazepam per os 0.03 mg kg^−1^ 1 hour before surgery (patients > 80 years with lorazepam 0.015 mg kg^−1^).

After 5 minutes of pre-oxygenation (FiO_2_ = 1.0), general anesthesia will be induced with a combination of remifentanil 0.5 μg kg^−1^ min^−1^ followed by a bolus of intravenous propofol 0.5–1 mg kg^−1^. Tracheal intubation will be facilitated by the bolus administration of cisatracurium (0.2 mg kg^−1^). Afterwards, the sealed randomization envelopes will be opened and patients will be randomly allocated to the two treatment groups in which general anesthesia will be maintained with either:xenon 40–60 % in oxygen (FiO_2_ = 0.5–0.6) (xenon-group), orsevoflurane 1.0–1.4 % (FiO_2_ = 0.5–0.6) (sevoflurane-group)

In both groups, anesthetic concentrations will be titrated according to the clinical observation of vegetative signs for the depth of anesthesia (including heart rate (HR), blood pressure, sweating, etc.) and to the instantaneously registered electroencephalogram (EEG)-monitoring in order to reach a bispectral index (BIS) value between 40 and 60. Cisatracurium will be administered at the induction of anesthesia. Further curarization will be left upon the discretion of the attending anesthesiologist.

Analgesia will be achieved with a continuous infusion of remifentanil (0.15–0.25 μg kg^−1^ h^−1^), starting after induction of anesthesia. The dose of remifentanil will be adjusted by increments of 0.05 μg kg^−1^ min^−1^ when the patient develops sweating, shows spontaneous movements and/or a sudden increase in HR or arterial pressure by more than 20 % [33]. *During the CPB period*, the investigational treatment will be discontinued in both groups and replaced with a target-controlled infusion (TCI) of propofol with calculated plasma concentrations of 1–2 μg ml^−1^ that will be titrated according to the BIS-monitoring. After completion of surgery, the interventional treatment will be stopped, and a bolus of intravenous (IV) piritramide 0.2 mg kg^−1^ will be given. Patients will be transferred to the ICU under mono-sedation with propofol.

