### Monitoring and hemodynamic management

Hemodynamic and respiratory monitoring will be provided according to our institutional routine including the placement of an arterial, a central venous and a pulmonary artery catheter. Whenever available, the following parameters will be recorded every 15 minutes from the pre-anesthetic period to the end of surgery: peripheral oxygen saturation (SpO_2_), invasive arterial blood pressure (IBP), HR, central venous pressure (CVP), cardiac output (CO), mixed venous oxygen saturation (SvO_2_), mean pulmonary artery pressure (MPAP), fraction of inspired oxygen (FiO_2_), end-tidal carbon dioxide (etCO_2_), body temperature, BIS, urine output, blood loss. Additionally, cerebral tissue oxygenation (rSO_2_) will be assessed by near-infrared spectroscopy (NIRS). Besides, transesophageal echocardiography (TEE) will be performed during anesthesia according to our institutional standards. Fixed measurements will be achieved for blood gas and a complete hemodynamic profile at the following time points: T0 = prior to induction, T1 = after induction, T2 = after sternotomy, T3 = after weaning from CPB, T4 = after sternal closure and T5 = end of surgery.

Intraoperative hemodynamic management will be standardized according to our clinical routine. Basic fluid substitution will be performed with 1 ml kg^−1^ h^−1^ balanced crystalloid solution. Hemodynamic stability will be defined as cardiac index > 2.5 L min^−1^ m^−2^, SvO_2_ > 70 % and mean arterial blood pressure of > 65 mmHg (between 50 and 60 mmHg during CPB). In case of hypovolemia (as detected by TEE or visual inspection of the heart), colloid solutions (gelatin) will be infused. Packed red blood cells (PC) will be transfused when the hemoglobin content is less than 8.0 g dL^−1^. A norepinephrine infusion will be administered when hemodynamic stabilization cannot be achieved despite adequate volume loading. The administration of inotropes, vasodilators, PC, fresh frozen plasma (FFP) and platelets will be left at the discretion of the attending anesthesiologist.

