### Cardiopulmonary bypass

CPB will be performed in mild to moderate hypothermia on a conventional CPB circuit with cardiac arrest induced by antegrade or retrograde infusion of cold crystalloid cardioplegic solution. Extracorporeal circulation will be performed with a pump flow of 2.2–2.5 L min^−1^ m^−2^. Prior to CPB, 300–350 IU kg^−1^ heparin will be administered to achieve an activated clotting time of > 400 s. After weaning from CPB, heparin will be antagonized with protamine in a ratio of 1:1. Furthermore, propofol TCI will be stopped and the investigational treatment will be re-administered.

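### The xenon range (40–60 %) and the oxygen range (FiO2 0.5–0.6) cannot both hold: either the 60 % xenon ceiling or the 0.5 FiO2 floor is wrong

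*Protocol article*

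**What the plan says.** All of this is in the protocol article, Methods/Design.

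- **Gas mixture, xenon arm** (General anesthesia): "xenon 40–60 % in oxygen (FiO_2_ = 0.5–0.6) (xenon-group").
- **Gas mixture, control arm** (same section): sevoflurane "1.0–1.4 % (FiO_2_ = 0.5–0.6) (sevoflurane-group"), so one FiO2 range is set for both arms.
- **Titration** (same section): in both arms, "anesthetic concentrations will be titrated according to the clinical observation of vegetative signs for the depth of anesthesia" and to the EEG monitor, "in order to reach a bispectral index (BIS) value between 40 and 60". Some signs of light anesthesia also have an opioid response: "The dose of remifentanil will be adjusted by increments of 0.05" μg/kg/min.
- **When the study gas runs**: during bypass, "the investigational treatment will be discontinued in both groups and replaced with a target-controlled infusion (TCI) of propofol"; afterwards, "propofol TCI will be stopped and the investigational treatment will be re-administered" (Cardiopulmonary bypass).
- **Exclusion criteria**: an intraoperative need for FiO2 above 50 % excludes a patient.
- **Recording** (Monitoring and hemodynamic management): the variables logged every 15 minutes, where available, include "fraction of inspired oxygen (FiO_2_), end-tidal carbon dioxide (etCO_2"_).

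**The concern.** The two ranges describe components of the same mixture, so they constrain each other. Read together, they give the anesthetist a maximum xenon setting that the stated oxygen minimum rules out. Because the concentration is titrated, the upper limit is a working instruction. Someone who wanted more than 50 % xenon would have to stop at 50 %, so that the printed maximum is never used, or let FiO2 fall below the printed minimum. The clearest case would be a BIS above 60 without the signs that call for more remifentanil. That case is an illustration; the article does not describe it.

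Two things are at stake. First, a reader cannot tell which maximum dose of the randomized drug was meant. Second, if the conflict were resolved patient by patient through a lower FiO2, this would happen in the xenon arm only. The plan sets the same oxygen range for both arms and lists the intraoperative hemodynamic and respiratory profile as a secondary endpoint, so an oxygen difference between arms would bear on a planned comparison.

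**Working it through.** **Inputs** (General anesthesia): xenon 40–60 %; FiO2 0.5–0.6, i.e. 50–60 % oxygen.

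**Constraint**: xenon % + oxygen % ≤ 100. This is the lenient form, since it allows some other gas to make up a remainder.

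**Step 1. Totals at the stated FiO2 limits, and the highest FiO2 each xenon setting allows (1 − xenon fraction)**

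| Xenon | Total at FiO2 0.5 | Total at FiO2 0.6 | Highest possible FiO2 |
|---|---|---|---|
| 40 % | 90 % | 100 % | 0.60 |
| 45 % | 95 % | 105 % | 0.55 |
| 50 % | 100 % | 110 % | 0.50 |
| 55 % | 105 % | 115 % | 0.45 |
| 60 % | 110 % | 120 % | 0.40 |

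Above 50 % xenon, no permitted FiO2 works. The shortfall against the 0.5 floor is 0.50 − 0.45 = 0.05 at 55 % xenon and 0.50 − 0.40 = 0.10 at 60 %.

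**Step 2. Share of the range affected.** Stated width: 60 − 40 = 20 points. Deliverable: 50 − 40 = 10 points. Not deliverable: 20 − 10 = 10 points.

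**Step 3. Can the printed pair be reproduced by treating one gas as the balance of the other?**

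- Xenon as the balance of FiO2 0.5–0.6: 1 − 0.6 = 0.40 to 1 − 0.5 = 0.50, i.e. xenon 40–50 %, not 40–60 %.
- Oxygen as the balance of xenon 40–60 %: 1 − 0.6 = 0.40 to 1 − 0.4 = 0.60, i.e. FiO2 0.4–0.6, not 0.5–0.6.

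Neither gives the printed pair. In both cases the low-xenon end fits exactly (40 % + 60 % = 100 %), and only the other end fails. That is the pattern expected from one wrong limit.

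**Step 4. Does another part of the article reconcile the two?** Pre-oxygenation at FiO2 1.0 is stated separately and precedes opening of the envelope, so it does not. During bypass the study gas is off, so the conflict is confined to the periods before and after bypass. Nothing assigns the two ranges to different periods, and nothing says which takes precedence.

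**Step 5. Which limit is wrong?** The exclusion criterion bears on this. A trial that turns away patients needing more than 50 % oxygen seems to want room to run at 50 % or less, which would fit FiO2 0.4–0.6. With FiO2 0.5–0.6, every setting except exactly 0.50 lies above that threshold. But needing more than 50 % oxygen differs from being given it by protocol, so the criterion is evidence and not proof.

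**Step 6. How many patients?** The xenon arm is 190 / 2 = 95 patients. The article gives no frequency for settings above 50 %, so the number is anywhere from 0 to about 95. That is only the size of the arm, not an estimate.

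**Step 7. Sample size.** The continuity-corrected two-proportion calculation for 40 % against 20 % returns the stated 91 per group. The gas ranges do not enter it.

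**The case against.** The best case on the other side is that this has little consequence. An impossible mixture cannot be delivered, so no patient can receive one. Xenon 40–50 % is usable as printed, remifentanil covers some signs of light anesthesia, the study gas is off during bypass, postoperative outcomes are assessed by blinded investigators (Limitations), and FiO2 is logged, so departures would largely be visible. All of this stands, and it is why the severity is low. It does not make the printed pair correct. Nor is this a detail left to a fuller document, because the article states both limits and they conflict.

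A reader might also infer that the 60 % ceiling is the error and that xenon should simply be capped at 50 %. The documents do not support that. The exclusion criterion points at least as much to the FiO2 floor. If 60 % was intended, capping at 50 % would lower the maximum dose of the experimental drug, which is as substantive as lowering the oxygen floor. The opposite inference, that the exclusion criterion proves the FiO2 range is misprinted, also goes too far, for the reason given in step 5 of the working.

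**Conclusion.** Wrong as written, low severity. The xenon range and the FiO2 range are incompatible above 50 % xenon, which removes 10 of the 20 points of the stated range. Either the 60 % ceiling or the 0.5 floor must change, and the article does not settle which. The arithmetic rests only on the printed ranges and on gas fractions not exceeding 100 %.

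A reader might infer that the xenon treatment cannot be given as described, or that the trial's main result is compromised. Neither follows. Part of the range is deliverable, and sample size, power and the primary analysis are unaffected. An oxygen imbalance between arms is a possibility only if anesthetists go above 50 % xenon by lowering FiO2, and nothing in the article shows whether or how often they would.

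**What to change.** The sponsor confirms which limit was intended and replaces the pair with one of these:

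- xenon 40–50 % with FiO2 0.5–0.6; or
- xenon 40–60 % with FiO2 0.4–0.6.

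Whichever is chosen, the same FiO2 range should be printed for the sevoflurane arm so that oxygen exposure stays matched. The first option changes one range; the second changes the FiO2 range in both arms. In making the choice, the sponsor should check it against the FiO2 exclusion criterion.

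Either change is reported to the ethics committee, as Study registration provides. If it only restores what was intended, it is a correction. If it alters the intended xenon dose or the intended oxygen floor, it should be handled as an amendment. This applies equally to both options.

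The trial report should also give the recorded FiO2 by arm. No extra patients, procedures or data collection are needed.

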### Monitoring and hemodynamic management

Hemodynamic and respiratory monitoring will be provided according to our institutional routine including the placement of an arterial, a central venous and a pulmonary artery catheter. Whenever available, the following parameters will be recorded every 15 minutes from the pre-anesthetic period to the end of surgery: peripheral oxygen saturation (SpO_2_), invasive arterial blood pressure (IBP), HR, central venous pressure (CVP), cardiac output (CO), mixed venous oxygen saturation (SvO_2_), mean pulmonary artery pressure (MPAP), fraction of inspired oxygen (FiO_2_), end-tidal carbon dioxide (etCO_2_), body temperature, BIS, urine output, blood loss. Additionally, cerebral tissue oxygenation (rSO_2_) will be assessed by near-infrared spectroscopy (NIRS). Besides, transesophageal echocardiography (TEE) will be performed during anesthesia according to our institutional standards. Fixed measurements will be achieved for blood gas and a complete hemodynamic profile at the following time points: T0 = prior to induction, T1 = after induction, T2 = after sternotomy, T3 = after weaning from CPB, T4 = after sternal closure and T5 = end of surgery.

Intraoperative hemodynamic management will be standardized according to our clinical routine. Basic fluid substitution will be performed with 1 ml kg^−1^ h^−1^ balanced crystalloid solution. Hemodynamic stability will be defined as cardiac index > 2.5 L min^−1^ m^−2^, SvO_2_ > 70 % and mean arterial blood pressure of > 65 mmHg (between 50 and 60 mmHg during CPB). In case of hypovolemia (as detected by TEE or visual inspection of the heart), colloid solutions (gelatin) will be infused. Packed red blood cells (PC) will be transfused when the hemoglobin content is less than 8.0 g dL^−1^. A norepinephrine infusion will be administered when hemodynamic stabilization cannot be achieved despite adequate volume loading. The administration of inotropes, vasodilators, PC, fresh frozen plasma (FFP) and platelets will be left at the discretion of the attending anesthesiologist.

